# Document versions

| **No** | **Version No.** | **Version Date** | **변경내용** |
| --- | --- | --- | --- |
| 1 | 1.0 | 2023.09.18 | First Version |
|  |  |  |  |

# Abbreviation

| **Abbreviation** | **Definition** |
| --- | --- |
| ALP | Alkaline Phosphatase |
| ALT | Alanine Aminotransferase |
| ANOVA | Analysis of Variance |
| AST | Aspartate Aminotransferase |
| BUN | Blood Urea Nitrogen |
| CBC | Complete Blood Count |
| CRF | Case Report Form |
| CSS | Cough Symptom Score |
| FAS | Full Analysis Set |
| GERDQ | Gastroesophageal reflux disease questionnaire |
| GGT | Gamma-glutamyl transpeptidase |
| HARQ | Hull Airway Reflux (hypersensitivity) Questionnaire |
| HCG | Human Chorionic Gonadotropin |
| ITT | Intention-to-treat |
| LCQ-K | Leicester Cough Questionnaire - Korean |
| NCS | Not clinically significant |
| PP | Per Protocol |
| RBC | Red Blood Cell |
| T-bilirubin | Total Bilirubin |
| U/A | Urinalysis |
| WBC | White Blood Cell |

# SYNOPSIS

| Title of the clinical inves-tigation | Efficacy and safety of Ojeok-san plus Saengmaek-san for gastroesophageal reflux-induced chronic cough: a randomized, double-blind, placebo-controlled, parallel, multicenter, investigator-initiated clinical trial |
| --- | --- |
| Objective | This study is a randomized, double-blind, placebo-controlled, parallel, multi-center, investigator-initiated clinical trial to assess the efficacy, safety, and economic value of OJS plus SMS compared to placebo in patients with GERC. |
| Princi-pal investigator /Investigational Site | 1. [name]/ Kyung Hee University Korean Medicine Hospital  2. [name]/ Gangdong Kyung Hee University Korean Medicine Hospital  3. [name]/ Daejeon University Daejeon Korean Medicine Hospital  4. [name]/ Pusan National University Korean Medicine Hospital  5. [name]/ Catholic Kwangdong University International St. Mary's Hospital |
| Participants | Gastroesophageal reflux-induced chronic cough |
| Investigational Product | 1. OJS plus SMS   \| ***Ojeok-san*** \|  \| \| --- \| --- \| \| Atractylodis Rhizoma \| 0.95 \| \| Ephedrae Herba \| 0.2 \| \| Citri Unshius Pericarpium \| 0.4 \| \| Magnoliae Cortex \| 0.08 \| \| Platycodonis Radix \| 0.43 \| \| Aurantii Immaturus Fructus \| 0.31 \| \| Angelicae Gigantis Radix \| 0.37 \| \| Zingiberis Rhizoma \| 0.22 \| \| Paeoniae Radix \| 0.27 \| \| Poria Sclerotium \| 0.02 \| \| Cnidii Rhizoma \| 0.3 \| \| Angelicae Dahuricae Radix \| 0.31 \| \| Pinelliae Tuber \| 0.22 \| \| Cinnamomi Cortex \| 0.04 \| \| Glycyrrhizae Radix et Rhizoma \| 0.2 \| \| Zingiberis Rhizoma Recens \| 0.03 \| \| Total \| 4.35 \| \| ***Saengmaek-san*** \|  \| \| Liriopis Tuber \| 0.75 \| \| Ginseng Radix \| 0.30 \| \| Schisandrae Fructus \| 0.36 \| \| Total \| 1.41 \|   2. Placebo  Placebos do not contain any of the active ingredients, OJS or SMS, and are composed of starch, lactose, and coloring and flavoring agents. |
| Methods | [figure not shown]  This study is a randomized, double-blind, placebo-controlled, parallel, multi-center, investigator-initiated clinical trial to assess the efficacy, safety, and economic value of OJS plus SMS compared to placebo in patients with GERC. The trial will be conducted at five hospitals in South Korea: Kyung Hee University Korean Medicine Hospital, Gangdong Kyung Hee University Korean Medicine Hospital, Daejeon University Daejeon Korean Medicine Hospital, Pusan National University Korean Medicine Hospital, and Catholic Kwangdong University International St. Mary's Hospital. After participants voluntarily signed a written informed consent, they will be screened for eligibility assessment, and those who meet the inclusion criteria will be enrolled for the next 8 weeks of the trial period (Fig.1). A total of 138 participants will be enrolled in this study from January, 2024. Participants will be allocated to either the OJS plus SMS group or the placebo group in a 1:1 ratio and will be asked to administer the investigational medicine three times a day for 6 weeks. For the evaluation of efficacy, safety, and economic assessments, participants will visit every 2 weeks until the last follow-up visit on week 8. |
| Sample Size | \| OJS plus SMS group \| Placebo group \| Total \| \| --- \| --- \| --- \| \| 69 \| 69 \| 138 \| |
| Inclusion criteria | 1. Aged 19-65 years 2. Subjects who have had a history of cough continuously for > 8 weeks 3. Subjects who had been diagnosed with GERD within the last 1 year (those who submitted documents diagnosed with reflux esophagitis at other hospitals or prescribed reflux esophagitis medicines for more than 4 weeks) 4. Subjects who consent to participate |
| Exclusion criteria | 1. Present with abnormal findings on chest radiography, pulmonary function test, or nasal endoscopy that might lead to cough. 2. Diagnosis of acute respiratory diseases (including upper respiratory tract disorders) within the previous month. 3. Presence of postnasal drip syndrome 4. Diagnosis of chronic respiratory diseases (e.g., chronic obstructive pulmonary disease, bronchial asthma, bronchiectasis, interstitial lung disease, and other chronic respiratory diseases) within the last 2 years 5. Diagnosed with Los Angeles classification system grade C or higher GERD within the past year 6. Symptoms indicative of malignant disease within the GI tract (e.g., severe dysphagia, bleeding, weight loss, anemia, and bloody stools) 7. History of esophagostenosis, esophageal varices, Barrett’s esophagus, peptic ulcer or gastrointestinal bleeding, and Zollinger-Ellison syndrome. 8. History of surgical or endoscopic anti-reflux treatment 9. Treatment with angiotensin-converting enzyme inhibitor during the previous 4 months 10. Treatment with cough medicines, glucocorticoids, leukotriene receptor antagonists, anticholinergic drugs, long-acting β2-agonists within the previous 2 weeks 11. Treatment with antihistamines within the previous 2 weeks 12. Treatment with PPIs, histamine receptor antagonists, mucosa-protective agents, GI motility promoters, antacids, antidepressants, anxiolytics, and lower esophageal sphincter agonists within the previous 2 weeks 13. Treatment with digitalis, mineralocorticoids, anticoagulants, and high-dose aspirin (≤325 mg is allowed) within the previous 4 weeks 14. Treatment with potassium-containing drugs, licorice-containing drugs, glycyrrhizinic acid or its salt-containing drugs, loop diuretics (furosemide, ethacrynic acid), or thiazide diuretics (trichloromethiazide) within the previous four weeks 15. A lifetime smoking history of ≥20 packs (400 cigarettes) 16. Body mass index < 18.5 kg/m^2^ 17. Aspartate aminotransferase (AST) or alanine aminotransferase (ALT) level at least twofold higher than the upper limit of normal or an eGFR ≤ 60 mL/min/1.73㎡ 18. Unregulated hypertension (high blood pressure of 160 mmHg in the condenser or high blood pressure exceeding 100 mmHg in a relaxation period > 3 min) 19. Active infection requiring systemic antibiotic therapy 20. Blood-clotting disorder 21. Hepatitis B (active) or hepatitis C, chronic liver disease 22. History of cerebrovascular accident (CVA) 23. History of malignant tumors (e.g., lung or esophageal cancer) within the last five years 24. History of drug or alcohol abuse 25. Allergies or sensitivities to the experimental medicine/placebo 26. Pregnant or breastfeeding 27. Subjects who did not agree to use contraception by medically permitted methods 28. Subjects who have participated in clinical trials within the past month 29. Subjects who are judged by the investigators to be inappropriate for the clinical trial |
| Efficacy Outcome Measures | - **Primary efficacy outcome**   - Cough Diary Score (CDS)   - **Secondary efficacy outcome**   1. Cough VAS  2. Leicester Cough Questionnaire – Korean version (LCQ-K)  3. Gastroesophageal reflux disease questionnaire (GERDQ)  4. Hull Airway Reflux Questionnaire (HARQ)  5. 5-level EuroQol 5-dimensional questionnaire (EQ-5D-5L)  6. Pattern Identification for Chronic Cough Questionnaire (PICCQ)  7. Pattern Identification for GERD |
| Safety Outcome Measures | - Adverse Events - Vital Signs - Laboratory tests - EKG |

# Schedule of enrolment, interventions, and assessments

|  | **STUDY PERIOD** | | | | | |
| --- | --- | --- | --- | --- | --- | --- |
|  | **Enrolment** | **Allocation** | **Post-allocation** | | | **Follow-up** |
| **VISIT** | ***1*** | **2** | ***3*** | ***4*** | ***5*** | ***6*** |
| **TIMEPOINT** | ***-2~1 week*** | **0** | ***2 weeks ± 3days*** | ***4 weeks ± 3days*** | ***6 weeks ± 3days*** | ***8 weeks ± 3days*** |
| **ENROLMENT:** |  |  |  |  |  |  |
| Eligibility screen | X |  |  |  |  |  |
| Informed consent | X |  |  |  |  |  |
| Demographics | X |  |  |  |  |  |
| Medical and  treatment history | X |  |  |  |  |  |
| Physical examination | X |  |  |  |  |  |
| Vital sign | X | X | X | X | X | X |
| Chest X-ray | X | X | X | X | X | X |
| Pulmonary Function Test | X |  |  |  |  |  |
| FeNO | X |  |  |  |  |  |
| Nasal Endoscopy | X |  |  |  |  |  |
| PNS x-ray (if needed) | X |  |  |  |  |  |
| EKG | X |  |  |  |  |  |
| Laboratory tests | X |  |  |  | X |  |
| Pregnancy Test | X |  |  |  |  |  |
| Allocation |  | X |  |  |  |  |
| **INTERVENTIONS:** |  |  |  |  |  |  |
| OJS plus SMS |  |  |  |  |  |  |
| Placebo |  |  |  |  |  |  |
| **ASSESSMENTS:** |  |  |  |  |  |  |
| Cough Symptom Score | X | X | X | X | X | X |
| Cough VAS | X | X | X | X | X | X |
| LCQ-K |  | X | X | X | X | X |
| GERDQ |  | X | X | X | X | X |
| HARQ |  | X | X | X | X | X |
| Pattern Identification for Chronic Cough Questionnaire | X | X |  |  |  |  |
| Pattern Identification for GERD |  | X |  |  |  |  |
| EQ-5D-5L |  | X | X | X | X | X |
| Abdominal Examination |  | X |  |  |  |  |
| WPAI:SHP |  | X | X | X | X | X |
| Adverse events |  | X | X | X | X | X |
| Compliance test |  |  | X | X | X |  |

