## Exclusion Criteria

1. Present with abnormal findings on chest radiography, pulmonary function test, or nasal endoscopy that might lead to cough.
2. Diagnosis of acute respiratory diseases (including upper respiratory tract disorders) within the previous month.
3. Presence of postnasal drip syndrome
4. Diagnosis of chronic respiratory diseases (e.g., chronic obstructive pulmonary disease, bronchial asthma, bronchiectasis, interstitial lung disease, and other chronic respiratory diseases) within the last 2 years
5. Diagnosed with Los Angeles classification system grade C or higher GERD within the past year
6. Symptoms indicative of malignant disease within the GI tract (e.g., severe dysphagia, bleeding, weight loss, anemia, and bloody stools)
7. History of esophagostenosis, esophageal varices, Barrett’s esophagus, peptic ulcer or gastrointestinal bleeding, and Zollinger-Ellison syndrome.
8. History of surgical or endoscopic anti-reflux treatment
9. Treatment with angiotensin-converting enzyme inhibitor during the previous 4 months
10. Treatment with cough medicines, glucocorticoids, leukotriene receptor antagonists, anticholinergic drugs, long-acting β2-agonists within the previous 2 weeks
11. Treatment with antihistamines within the previous 2 weeks
12. Treatment with PPIs, histamine receptor antagonists, mucosa-protective agents, GI motility promoters, antacids, antidepressants, anxiolytics, and lower esophageal sphincter agonists within the previous 2 weeks
13. Treatment with digitalis, mineralocorticoids, anticoagulants, and high-dose aspirin (≤325 mg is allowed) within the previous 4 weeks
14. Treatment with potassium-containing drugs, licorice-containing drugs, glycyrrhizinic acid or its salt-containing drugs, loop diuretics (furosemide, ethacrynic acid), or thiazide diuretics (trichloromethiazide) within the previous four weeks
15. A lifetime smoking history of ≥20 packs (400 cigarettes)
16. Body mass index < 18.5 kg/m^2^
17. Aspartate aminotransferase (AST) or alanine aminotransferase (ALT) level at least twofold higher than the upper limit of normal or an eGFR ≤ 60 mL/min/1.73㎡
18. Unregulated hypertension (high blood pressure of 160 mmHg in the condenser or high blood pressure exceeding 100 mmHg in a relaxation period > 3 min)
19. Active infection requiring systemic antibiotic therapy
20. Blood-clotting disorder
21. Hepatitis B (active) or hepatitis C, chronic liver disease
22. History of cerebrovascular accident (CVA)

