# Trial Design

## Procedure

This study is a randomized, double-blind, placebo-controlled, parallel, multi-center, investigator-initiated clinical trial to assess the efficacy, safety, and economic value of OJS plus SMS compared to placebo in patients with GERC. The trial will be conducted at five hospitals in South Korea: Kyung Hee University Korean Medicine Hospital, Gangdong Kyung Hee University Korean Medicine Hospital, Daejeon University Daejeon Korean Medicine Hospital, Pusan National University Korean Medicine Hospital, and Catholic Kwangdong University International St. Mary's Hospital. After participants voluntarily signed a written informed consent, they will be screened for eligibility assessment, and those who meet the inclusion criteria will be enrolled for the next 8 weeks of the trial period (Fig.1). A total of 138 participants will be enrolled in this study from January, 2024. Participants will be allocated to either the OJS plus SMS group or the placebo group in a 1:1 ratio and will be asked to administer the investigational medicine three times a day for 6 weeks. For the evaluation of efficacy, safety, and economic assessments, participants will visit every 2 weeks until the last follow-up visit on week 8.

[figure not shown]

<임상시험 진행 흐름>

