# Dropout and Early termination criteria

At any time during the clinical trial, participants can voluntarily withdraw from the clinical trial. Additionally, anyone who meets any of the following conditions will be dropped out from the trial at the discretion of investigators:

1. found to violate the inclusion and exclusion criteria after screening visit,
2. in the case where the participant requests discontinuation of the trial or refuses the treatment due to unsatisfactory treatment effects during the trial period,
3. in the case where the participant cannot be tracked during the trial period,
4. when it is judged by investigators that trial participation is no longer possible due to an adverse reaction or a concomitant disease,
5. in the case of taking prohibited drugs that may affect the trial result without the instruction of investigators during the trial period,
6. when it is judged that the effect evaluation of the clinical trial is not appropriate because the overall compliance with the investigational products is less than 70% in YGJ and PWS groups,
7. when the participant violates the trial plan, and it is difficult for the participant to continue the trial, and
8. when investigators judged that the progress of the clinical trial is no more appropriate.

In principle, this clinical trial is finalized when the registration of the planned number of participants is completed and the completeness of the collected data is secured. However, in the following cases, this clinical trial can be discontinued: (1) when the harmfulness of the supplied investigational products is found, (2) if moderate or severe adverse events judged to be related to investigational products occur in more than 25% of all participants, and (3) in the case when the targeted participants are not registered even though a sufficient recruitment period has been given.

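### Both visit schedules mark a chest X-ray at all six visits although its only stated use is eligibility; a lesser point is that EKG, a listed safety outcome, is scheduled only before dosing

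*Protocol*

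**What the plan says.** The visit schedule appears twice in the protocol: after the synopsis (Schedule of enrolment, interventions, and assessments) and under Procedure, Timetable. The two tables agree. Each marks chest X-ray at all six visits: "Chest X-ray | X | X | X | X | X | X". The row directly above has the same pattern: "Vital sign | X | X | X | X | X | X".

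Outside the tables, chest radiography is mentioned only in exclusion criterion 1 (synopsis and Exclusion Criteria), which rules out people who "Present with abnormal findings on chest radiography, pulmonary function test, or nasal endoscopy that might lead to cough". The other two tests in that criterion are scheduled once, at Visit 1: "Pulmonary Function Test | X" and "Nasal Endoscopy | X". So is the only other radiograph: "PNS x-ray (if needed) | X".

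EKG is the reverse case. The synopsis and the Safety Outcomes section both list it as a safety outcome, yet both tables mark it at Visit 1 only. Laboratory tests, listed beside it, are marked at Visits 1 and 5. The paragraph under the Safety Outcomes list describes vital signs, adverse events and laboratory tests, and mentions neither EKG nor chest X-ray.

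**The concern.** The schedule is what sites work from. A procedure marked at every visit is an instruction to do it at every visit. Here the instruction is for five chest films after screening, although the text uses the film only to decide eligibility, and eligibility is settled at Visit 1. A site that follows the table exposes participants to radiation for no stated reason. A site that skips the films departs from the written schedule. The pregnancy test is also marked at Visit 1 only, so the later films would be taken without a scheduled repeat test, although participants must agree to contraception.

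The EKG point concerns data. A safety outcome recorded only before the first dose cannot show anything about treatment, so the list promises something that the schedule cannot deliver.

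**Working it through.** **Inputs**

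- Visit marks: the two schedule tables.
- Number enrolled: "A total of 138 participants will be enrolled in this study" (Trial Design, Procedure).
- Planned dropout: 20% (Sample size).

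**The plan's own figure.** The sample size reproduces with a difference of 0.75, SD 1.4, power 0.80 and two-sided α 0.05:

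- n per group = 2 × (1.96 + 0.8416)² × 1.4² / 0.75² ≈ 54.7, rounded up to 55.
- Allowing for dropout: 55 / 0.8 = 68.75, rounded up to 69 per group, 138 in total.

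The finding does not depend on this. The 138 is used only for counting films.

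**Schedule marks against stated purpose**

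| Procedure | Stated use | Marked at | Marks |
| --- | --- | --- | --- |
| Chest X-ray | Exclusion criterion 1 | Visits 1–6 | 6 |
| Pulmonary function test | Exclusion criterion 1 | Visit 1 | 1 |
| Nasal endoscopy | Exclusion criterion 1 | Visit 1 | 1 |
| PNS x-ray (if needed) | None given in the text | Visit 1 | 1 |
| Vital signs | Safety outcome, every visit | Visits 1–6 | 6 |
| Laboratory tests | Safety outcome, before and after dosing | Visits 1 and 5 | 2 |
| EKG | Listed safety outcome | Visit 1 | 1 |

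Chest X-ray has the purpose of the screening tests and the marks of the vital-sign row above it. That suggests the marks were copied across. This is an inference; the document does not give the cause.

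**Count of films**

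- As written: 6 × 138 = 828.
- Visit 1 only: 1 × 138 = 138.
- Excess: 828 − 138 = 5 × 138 = 690. This is a ceiling, because it assumes that all 138 attend every visit.
- Completers only, at 20% dropout: 0.8 × 138 ≈ 110, and 110 × 5 = 550. Participants who leave part-way would add some films to this.

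**EKG.** There is one mark before dosing and none at Visits 3–6, so no change from baseline can be computed from scheduled recordings. One EKG added at Visit 5 would mean at most 1 × 138 = 138 recordings.

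**The case against.** The strongest reply is that no sentence in the protocol contradicts the X-ray row. The two tables agree, and nothing says that the film is for screening only. Cough is the endpoint, so films to detect intercurrent lung disease are conceivable. The dropout criteria also allow withdrawal for concomitant disease and of anyone "found to violate the inclusion and exclusion criteria after screening visit".

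It is true that this is a procedure without a purpose rather than two statements in open conflict. But the dropout criteria permit withdrawal when a problem is found; they do not call for routine films. Monitoring for lung disease is nowhere stated as an aim. It would hardly explain a film at Visit 2, before dosing and shortly after screening. Agreement between the tables shows little if one was copied from the other.

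Two cautions on impact stand. The counts describe the schedule, not films known to have been taken. Also, the version table lists only 1.0, while the ethics section refers to an approved version 1.2, so the schedule in use at sites may differ from this text.

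On EKG, the safety paragraph leaves it out of what is evaluated during the trial, which fits a screening test wrongly placed in the outcome lists. Pointing the other way, the product contains Ephedrae Herba and Glycyrrhizae Radix, and exclusions 13 and 14 bar digitalis and licorice-containing drugs. The protocol does not tie any of this to EKG, so it is weak evidence for a missing Visit 5 mark. The document does not settle which side is wrong.

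**Conclusion.** The concern holds. As written, the schedule calls for five chest radiographs per completer with no stated purpose: at most 690 over 138 participants, and about 550 from expected completers alone. These figures assume that sites follow the tables as printed; whether any have done so cannot be known from the protocol. The marks and the missing purpose are certain, while the copying slip is only the likely explanation.

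The EKG mismatch is real but smaller. Cardiovascular and electrolyte safety is still covered after dosing by vital signs and adverse events at the visits and by electrolytes at Visit 5. Neither point touches the primary outcome, the planned tests or the sample size. The correction should be made because the schedule governs what is done to participants.

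**What to change.** **Chest X-ray.** In both schedule tables, delete the marks at Visits 2–6 and keep Visit 1. If the sponsor did intend follow-up films, the protocol must state their purpose and justify the exposure; nothing in the present text does so.

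**EKG.** Make the lists and the schedule agree, according to the sponsor's intent:

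- (a) take EKG out of the safety outcomes in the synopsis and in Safety Outcomes, and describe it as a screening test; or
- (b) keep it as a safety outcome, add one mark at Visit 5 in both tables alongside the post-dose laboratory tests, and name EKG in the safety paragraph.

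**Cost.** A table and text correction by amendment. The X-ray change adds no procedure and removes up to five per participant. EKG option (a) adds none. Option (b) adds one recording per participant, at most 138.

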# **Title of the clinical investigation**

Efficacy and safety of Ojeok-san plus Saengmaek-san for gastroesophageal reflux-induced chronic cough: a randomized, double-blind, placebo-controlled, parallel, multicenter, investigator-initiated clinical trial

(Protocol Number: KIOM_22_GERC)

## Sponsor

Korea Institute of Oriental Medicine

# Background

Gastroesophageal reflux-induced chronic cough (GERC) is among the most common extraesophageal manifestations of gastroesophageal reflux disease (GERD), with cough being observed in 30.5–34.9% of patients with GERD ^1^. GERD is also a major cause of chronic cough, along with the upper airway cough syndrome and cough-variant asthma ^2^. GERD and coughing affect each other, aggravating GERC. Under the current understandings, the mechanism by which gastroesophageal reflux induces cough is explained by reflux theory (micro-aspiration of the gastric refluxate into the respiratory tract), reflex theory (the stimulation of the esophageal-bronchial cough reflex mediated by the afferent nerves in the distal esophagus) ^3^, and esophageal dysmotility ^4^. However, a causal relationship between GERD and coughing has not yet been established.

Anti-reflux treatments of GERC, such as proton pump inhibitors (PPIs) and H2 antagonists, alone or in combination with promotility agents, are currently considered the standard therapy for GERC ^3^. However, recent studies have reported that more than one-third of patients do not respond to PPIs ^5^, and multiple reviews have found a lack of evidence regarding the use of empirical PPI therapy for GERC ^6^. These refractory cases of GERC are often observed in patients who do not have GERD symptoms such as heartburn and regurgitation, and are presumed to be due to non-acidic or weakly acidic reflux (4), which accounts for 80% of PPI-treated chronic cough cases ^7^. Recently, for refractory GERC, neuromodulators such as gabapentin and baclofen have been used in some studies; however, their efficacy remains unclear with regard to unnecessary adverse effects ^8^. Therefore, further studies are needed to develop a new, effective, and safe drug to manage GERC, including non-symptomatic refractory GERC.

In this study, we propose the herbal medicines Ojeok-san (OJS) plus Saengmaek-san (SMS) for the treatment of GERC as a new insight. Contrary to anti-reflux drugs, which have limitations in non-symptomatic GERC, we targeted the management of the cough reflex by modulating neurogenic airway inflammation and improving esophageal dysmotility. OJS and SMS are widely used in Korean Medicine to manage digestive, respiratory, and neurological disorders owing to their pharmacological activities ^9 10^. OJS exerts anti-inflammatory effects by decreasing the levels of pro-inflammatory cytokines ^11^ and analgesic effects by ameliorating visceral and somatic nociception ^12^. It has also been reported to reduce airway inflammation and pulmonary fibrosis, by suppressing the level of T helper type 2 cytokines, VEGF, and TGF-β1/Smad3 expressions ^13^. SMS, primarily used for dry cough, is known for its mucolytic effects on the respiratory tract ^14^, antioxidant and anti-inflammatory effects ^10^, and gastroprokinetic effects by regulating gastrointestinal (GI) motility and increasing the activity of the interstitial cells of Cajal ^15^. Taken together, we expect that OJS plus SMS can attenuate airway inflammation and regulate esophageal motility, thereby exerting its effects on GERC.

We found the potential effects of OJS plus SMS for GERC in our pilot study by showing significant differences in cough diary scores (CDS) compared to the placebo ^16^. By addressing the limitations of a previous pilot study, we designed a confirmatory, large-scale, multi-center clinical trial to evaluate the efficacy, safety, and economic value of OJS plus SMS in the treatment of GERC patients. We specified the diagnosis of GERD and the restricted conditions that could affect its safety and efficacy in patients with GERC. Secondary efficacy outcomes evaluating GERD-related symptoms, quality of life, and economic status were added to this trial. Overall, cough symptoms, airway hypersensitivity, GERD-related symptoms, and quality of life will be evaluated in this trial, and our study results will provide evidence for the use of OJS plus SMS in the treatment of GERC.

